## Abstract

**Background:**

Peripheral artery disease (PAD) can develop into critical limb ischemia (CLI), which is characterized by resting pain at rest, ulcerations, or gangrene, with a high risk of amputation. The optimum course of treatment at this point is arterial revascularization, although this has a significant financial cost and is not always feasible or successful in reducing pain, healing ulcers, or preventing amputations. In situations where traditional alternatives for treating PAD have been exhausted, recent developments in cell therapy may offer a viable substitute.

**Objective:**

The purpose of this study is to assess the safety and effectiveness of using expanded autologous adipose-derived stem cells (ASCs) in cellular therapy for the treatment of PAD patients who developed chronic artery ulcers.

**Methods:**

An open randomized clinical trial will be carried out with two groups of twenty patients with CLI: In group 1, 2g of abdominal adipose tissue will be taken to produce ASCs. These cells will then be expanded in a lab (cell processing center) for 14–21 days before being applied to the lesion using bio-dressings and perilesional subcutaneous injections. Group 2 will receive conventional treatment with hydrogel-based dressing. There will be regular clinical assessments, supplementary tests, and photo documentation. The main efficacy outcome will be partial or complete healing of the wound. Safety outcomes will be monitored for infections, gangrene, amputations, and death. Participants will be monitored for 90 days. Cases of major amputation of the studied limb will not be included. The results will be evaluated by an independent external evaluator who is blind to the groups. Considering the high prevalence and socioeconomic consequences related to CLI and limb amputation, this study is expected to provide a positive social and financial impact on the Brazilian Unified Health System.

ClinicalTrials.gov: NCT06326203.

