### Inclusion criteria

Ability to understand and accept written free informed consent form (ICF) (S2 File ICF in Portuguese and English).Both sexes, of any ethnic origin.Age between 18 and 90 years old at the time of signing the ICF.Absence of distal pulses of the affected lower limb (anterior tibialis, dorsalis pedis, and posterior tibialis).PAD with CLI, classified as Fontaine IV [27] or Rutherford 5 and 6 [28].Between 1 and 3 ulcers on the foot or distal third of the leg of at least 1 cm^2^ up to a maximum of 20 cm^2^ in area.Previous treatment with conventional dressings, antibiotic therapy, or debridement (if necessary) and no improvement in a minimum period of 3 weeks.Having an ankle-brachial index (ABI) < 0.9 for below-knee arteries (anterior tibial, dorsalis pedis, posterior tibial, and fibular) or ABI > 1.3 in one or more of those arteries in association with type 2 diabetes (disease duration > 5 years) [29,30].Not undergoing revascularization treatment or failed revascularization treatment in the last 12 months.Impossibility of arterial revascularization of the affected limb and/or incomplete revascularization of that limb (subjected to endovascular or surgical treatment that was unable to reestablish blow-knee perfusion), meaning exhaustion of all surgical therapies.Optimized drug treatment for PAD and comorbidities.Availability to attend medical appointments.

After the participant’s inclusion in the study, regardless of the group allocated, they will be sent to collect laboratory tests: blood glucose, glycated hemoglobin, total cholesterol, high-density lipoprotein (HDL), low-density lipoprotein (LDL), triglycerides, complete blood count, uric acid, urea, creatinine, C-reactive protein (CRP), sodium, potassium, and immunomodulatory cytokine profile.

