### Sample size

The sample calculation considered two independent samples with an estimated proportion of the ulcer healing rate of 75% for group 1, which will be treated with cell therapy, and 30% for group 2, which will be treated with hydrogel dressing. Assuming a test power of 80% and a significance level of 5% for a two-sided test, the sample was defined as 20 participants for group 1 and 20 participants for group 2 (1:1 allocation). This study was designed to be analyzed with intention to treat (ITT).

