### Primary outcomes

#### Safety.

Absence of major amputations (ankle, leg, or thigh).EfficacyTotal ulcer epithelialization and limb salvage rate (non-occurrence of a major amputation).

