#### Efficacy.

Improvement in limb perfusion [34]: Assessed by thermography [35,36] (significant increase in limb temperature > 0.3 ºC), vascular ultrasound with Doppler (flow wave characteristics and flow velocity incrementation), ABI [29,30] (increase in ABI value ≥ 0.15 for participants with ABI < 0.9), transcutaneous capnography [37] (incrementation ≥ 10% in O_2_ levels and/or decrease ≤ 10% in CO_2_ levels measured at the base of the hallux and the ankle, behind the medial malleolus) and WIfI (the Society for Vascular Surgery Lower Extremity Threatened Limb Classification System: risk stratification based on wound, ischemia, and foot infection) [38,39].Improvement in quality of life: assessed by the SF-36 scale (Medical Outcomes Study 36 – Item Short-Form Health Survey) [40].Reduction in pain: Assessed by the Visual Analogue Scale (VAS) [41] and reduction in the use of analgesics (quantitatively and qualitatively).Partial ulcer healing: Assessed by measuring epithelialization of the ulcer. The total ulcer area will be analyzed using the area measurement tool in the free software ImageJ™ [42,43].Improvement in health perception: Assessed by the EQ-5D scale by EuroQol Group [44].Clinical improvement: Observed through physiological (blood pressure) and laboratory parameters (glycemia, glycated hemoglobin, HDL, LDL, total cholesterol, triglycerides, leukogram, hematocrit, uric acid, urea, creatinine, CRP, sodium, potassium, alkaline phosphatase (ALP), alanine transaminase (ALT), aspartate transferase (AST), gamma-glutamyl transferase (GGT), bilirubin, total protein, albumin, prothrombin time (PT), partial thromboplastin time (PTT)).Formation of granulation tissue in the ulcer.Changes in the systemic inflammatory profile with a predominantly cellular immune response through analysis of immunomodulatory cytokines (Th1, Th2, and Th17) [45,46].

### 
Participant timeline

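### The primary efficacy outcome is defined differently in the abstract and the methods, and the 75% v 30% behind the sample size is tied to neither definition

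*Protocol article*

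**What the plan says.** Four places in the protocol article bear on the primary efficacy outcome.

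- **Abstract, Methods:** "The main efficacy outcome will be partial or complete healing of the wound". The follow-up given there is 90 days.
- **Primary outcomes:** the efficacy entry is total "ulcer epithelialization and limb salvage rate (non-occurrence of a major amputation"). The primary safety outcome in the same section is the absence of major amputation.
- **Secondary outcomes, Efficacy:** "Partial ulcer healing: Assessed by measuring epithelialization of the ulcer", with the area measured in ImageJ.
- **Sample size:** "an estimated proportion of the ulcer healing rate of 75% for group 1", against 30% in the control group. With 80% power and a two-sided 5% level, the section arrives at 20 participants per group.

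Three further places matter. The Inclusion criteria admit participants with "Between 1 and 3 ulcers on the foot or distal third of the leg". The Participant timeline places the closing assessment at 120 days. The Sample size and Statistics section sets 5% for all tests and mentions a Bonferroni coefficient without attaching it to any set of outcomes.

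**The concern.** The abstract and the methods disagree about what the trial is mainly meant to show. Partial healing counts towards the main outcome in one and is secondary in the other. Limb salvage is primary in one and absent from the main outcome in the other. Shortening does not explain this: a condensed abstract drops detail, but it does not move a secondary component into the main outcome.

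The Primary outcomes section leaves a second question open. Joining epithelialisation and limb salvage with a plain conjunction could mean a composite, two endpoints that must both succeed, or two endpoints of which either suffices. These have different error rates and different power.

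The sample size depends on the answer. Its healing rate is not labelled complete or partial, so a reader cannot tell which outcome the trial was sized for. In an open-label trial of 40 participants the primary efficacy outcome carries the conclusion, and two teams following this text could report different headline results.

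**Working it through.** **1. The passages side by side**

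| Component | Abstract | Primary outcomes | Secondary outcomes | Sample size |
|---|---|---|---|---|
| Complete healing | main | primary | – | not specified |
| Partial healing | main | – | secondary | not specified |
| Limb salvage | – | primary (efficacy); same event as primary safety | – | – |
| Time of final assessment | 90 days | not stated (120 days in Participant timeline) | not stated | not stated |

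No row for healing or limb salvage reads the same across the abstract and the outcome sections, and the Sample size column settles none of them.

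**2. Reproducing the plan's own figure**

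Inputs from the Sample size section: p1 = 0.75, p2 = 0.30, two-sided 5%, power 80%. The mean proportion is p̄ = (0.75 + 0.30)/2 = 0.525.

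n = [1.960·√(2p̄(1−p̄)) + 0.8416·√(p1(1−p1) + p2(1−p2))]² / (p1−p2)²

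= [1.960·√0.49875 + 0.8416·√0.3975]² / 0.45²

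= [1.384 + 0.531]² / 0.2025 = 18.1, so 19 per group.

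The stated 20 is consistent with this. At 20 per group, power is 84.1% by the same normal approximation. Exact enumeration over all 21 × 21 possible results gives 73.1% for Fisher's exact test and 82.3% for Pearson's chi-square, both of which the plan names. The arithmetic is sound, but it does not show which outcome the rates describe.

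**3. What a different outcome would do to power**

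The documents give no separate rates for complete healing and for partial-or-complete healing. The pairs below, other than the first, are assumptions. Power is by exact enumeration at 20 per group.

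| Rates | Fisher | Pearson |
|---|---|---|
| 75% v 30% (stated) | 73% | 82% |
| 60% v 30% | 35% | 46% |
| 50% v 20% | 41% | 53% |
| 60% v 20% | 65% | 75% |
| 90% v 60% | 49% | 62% |
| 85% v 50% | 57% | 69% |
| 90% v 50% | 74% | 84% |
| 90% v 45% | 84% | 91% |

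The three assumed pairs at or below the stated rates show what might happen if complete healing is rarer than 75% v 30%. The four higher pairs show what might happen if partial healing is counted and both rates rise. Power can fall, stay level or rise.

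**4. Error rate if there are two primary tests**

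If each of two outcomes is tested at 5% and either suffices, the nominal familywise error is 1 − 0.95² = 9.75% under independence, and at most 5% + 5% = 10% in general. Fisher's test is conservative at this size: by enumeration its actual type I error is about 1.2% to 2.5% for null rates of 10% to 50%. Two independent tests at 2.5% give 1 − 0.975² = 4.9%, so with Fisher the total stays below 5%. If both outcomes must succeed, there is no inflation.

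**The case against.** The strongest reply is that only the abstract is out of line. The methods rank the outcomes explicitly, one summary sentence disagrees, and a careful reader would follow the methods. The partial-healing threshold, the handling of two or three ulcers and the success rule for two endpoints are commonly left to an analysis plan or the full protocol, neither of which is shown. Evaluators and statisticians are also to receive the results blinded.

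Much of this stands. The missing threshold and the multiple-ulcer rule are not faults in themselves. What remains is that the document states two different main outcomes, and that its sample size is linked to neither. Later detail can refine a definition, but the protocol still has to say which outcome it was sized on.

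Three stronger readings are tempting and are not supported:

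- **That the sponsor means to choose the outcome after seeing the data.** The text leaves the choice open. It shows no such intent, and an unseen document may already fix the definition.
- **That the trial is underpowered.** A figure such as 49% comes from one assumed pair of rates; another plausible pair gives 84%. Part of any gap from 80% is also due to the test, since Fisher gives only 73% at the plan's own rates.
- **That the type I error is 9.75%.** That needs an either-suffices rule, independence and tests that reach their nominal 5%. The plan states no such rule and makes a vague mention of Bonferroni, and Fisher's test would keep the total below 5%.

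**Conclusion.** The point holds as a contradiction in the current text. The abstract, the Primary outcomes section and the Secondary outcomes section cannot all be followed, and the Sample size section does not say which outcome its 75% v 30% describes. Limb salvage also serves as both primary efficacy and primary safety, with its relation to epithelialisation left open.

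The sample-size arithmetic is not at fault. The consequence for power cannot be fixed from the documents: about 35% to 84% with Fisher's test across the assumed pairs above, against 73% for the stated rates. The consequence for type I error ranges from none to a nominal 9.75% (at most 10%), depending on the success rule and the test. The point should be settled before outcome data are analysed, because the trial's main conclusion depends on it.

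**What to change.** Name one participant-level primary efficacy outcome, in the same words, in the abstract, the Sample size section and the Primary outcomes section.

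- **Outcome.** Complete epithelialisation of all study ulcers, from the blinded image reading, fits the ranking already in the outcome sections. Count death or major amputation as not healed; this agrees with the Data collection plan, which treats both as endpoints and not as lost data.
- **Time.** State one day, after reconciling the 90 days in the abstract with the 120 days in the Participant timeline.
- **Other outcomes.** Keep partial healing secondary, as percent change in area. Make limb salvage a secondary efficacy outcome, with major amputation remaining the primary safety outcome.
- **Sample size.** State which definition of healing the 75% v 30% describes. The rates should not simply be attached to complete healing, because nothing in the document shows that they belong there. If they describe something else, give the expected rates for the chosen outcome and the resulting power at 20 per group.

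The cost is rewording in three places, plus a renewed justification of the rates if they do not match the outcome. No extra visits are needed. The downside is that partial responders no longer count in the headline result, and the stated power may become less favourable.

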## Introduction

Peripheral arterial disease (PAD) is a clinical manifestation of atherosclerotic disease in arteries that supply the limbs [1,2]. PAD of the lower limbs affects more than 230 million adults worldwide [3,4] and is often associated with other cardiovascular diseases like obstructive atherosclerotic disease of cerebral and coronary vessels, consequently increasing the risk of stroke and myocardial infarction [5,6].

The most urgent form of PAD is critical limb ischemia (CLI) which occurs when the arterial perfusion is severely impaired, leading to intense pain and the occurrence or worsening of ulcers that may be difficult to heal [7,8]. CLI affects between 11% and 20% of patients with PAD [9], and in extreme cases, can lead to gangrene of the extremities, which correlates with high cumulative rates of amputation and death [10].

The treatment of PAD and CLI is complex and involves a combination of medical therapies, endovascular interventions, and, in some cases, surgical bypasses [11–13]. Amputation-free survival may be challenging. Repeated vascular interventions may be necessary to maintain limb viability, sometimes exhausting the surgeon’s repertoire. Furthermore, many patients do not have the minimum clinical conditions to undergo surgical procedures, with persisting ulcers that are difficult to heal, generally resulting from traumas or minor amputations. Ultimately, after exhaustion of therapeutic options, due to the worsening quality of life and resting pain associated with CLI, amputations end up being the only alternative.

Recently, stem cell therapy [14–16] for the treatment of CLI has been presented as a promising alternative to improve ulcer healing and promote the regeneration of ischemic tissues [17–21]. Preliminary studies indicate that the application of stem cells can increase blood perfusion and reduce amputations, offering new hope for these patients [22–24]. In a systematic review study by Jiang et al [25], it was concluded that autologous stem cell therapy is effective and safe for improving chronic ulcer healing of the lower limbs, without serious adverse effects.

Therefore, the objective of this study is to evaluate the safety and efficacy of cellular therapy with autologous adipose-derived stem cells (ASCs) using perilesional subcutaneous injections and bio-dressings [26] over ulcers for patients with PAD in advanced-stage CLI. The results will be compared with a control group that will receive conventional hydrogel dressings (Dersani Hydrogel, Megalabs Pharmaceutical S.A. Rio de Janeiro – RJ, Brazil, registration number 80219190002). Data from this study may corroborate previous literature and support the development of cell therapy to offer a new alternative for patients with PAD and CLI.

## Method

### Study design

This is a phase I/II, single-center, randomized clinical trial (RCT), PROBE (Prospective Randomized Open, Blinded Endpoint), controlled to evaluate the safety and efficacy of using ASCs to treat injuries in patients with PAD and advanced-stage CLI. The study was designed to attend the guidance Standard Protocol Items: Recommendations for Interventional Trials for clinical trial protocols (SPIRIT). (S1 File SPIRIT checklist)

### Study location

The study will be conducted at the Clinical Hospital of the Medical School (HC-FMB), and the Clinical Research Unit (UPECLIN) of São Paulo State University (Unesp), Botucatu Campus. The ASCs will be prepared at the Cell Processing Center (CPC) of the Applied Biotechnology Laboratory in the same institution.

### Study population

The target population will be participants of both sexes with advanced-stage PAD and CLI of the lower limbs, without the possibility of effective revascularization.

### Clinical trials

Information about the study and results will be published in international journals and registered on the United States National Institutes of Health website: www.clinicaltrials.gov, and the registered protocol is “Cell Therapy for Lower Limb Ulcers in Patients With Critical Limb Ischemia” number NCT06326203. This is the first version of the protocol and was registered in clinical trials on 03/16/2024. The last release was made public on 12/04/2024.

### Inclusion criteria

Ability to understand and accept written free informed consent form (ICF) (S2 File ICF in Portuguese and English).Both sexes, of any ethnic origin.Age between 18 and 90 years old at the time of signing the ICF.Absence of distal pulses of the affected lower limb (anterior tibialis, dorsalis pedis, and posterior tibialis).PAD with CLI, classified as Fontaine IV [27] or Rutherford 5 and 6 [28].Between 1 and 3 ulcers on the foot or distal third of the leg of at least 1 cm^2^ up to a maximum of 20 cm^2^ in area.Previous treatment with conventional dressings, antibiotic therapy, or debridement (if necessary) and no improvement in a minimum period of 3 weeks.Having an ankle-brachial index (ABI) < 0.9 for below-knee arteries (anterior tibial, dorsalis pedis, posterior tibial, and fibular) or ABI > 1.3 in one or more of those arteries in association with type 2 diabetes (disease duration > 5 years) [29,30].Not undergoing revascularization treatment or failed revascularization treatment in the last 12 months.Impossibility of arterial revascularization of the affected limb and/or incomplete revascularization of that limb (subjected to endovascular or surgical treatment that was unable to reestablish blow-knee perfusion), meaning exhaustion of all surgical therapies.Optimized drug treatment for PAD and comorbidities.Availability to attend medical appointments.

After the participant’s inclusion in the study, regardless of the group allocated, they will be sent to collect laboratory tests: blood glucose, glycated hemoglobin, total cholesterol, high-density lipoprotein (HDL), low-density lipoprotein (LDL), triglycerides, complete blood count, uric acid, urea, creatinine, C-reactive protein (CRP), sodium, potassium, and immunomodulatory cytokine profile.

### Exclusion criteria

Pregnancy planning, being pregnant, or in the postpartum period.Healed ulcer during the screening.Signs of systemic infection, active infection, devitalized tissue (necrosis) of the arterial ulcer, or infection of surgical prostheses. Participants excluded by these criteria may be reevaluated for inclusion after successful treatment with antibiotics and removal of the infectious focus (including minor amputations such as toes or forefoot).Active cancer, chemotherapy, radiotherapy, or cancer in remission for less than 6 months.Use of colchicine or immunomodulators.Infectious diseases such as Human Immunodeficiency Virus (HIV), Hepatitis B Virus (HBV), Hepatitis C Virus (HCV), and Human T-cell lymphotropic Virus (HTLV).Major amputation (at ankle, leg, or thigh level) of the limb to be studied.Diagnosed Coronavirus Disease (COVID-19) for less than 4 weeks.

### Participant replacement

Participants excluded during the screening period – which corresponds to the interval between the initial assessment and first reassessment of the arterial ulcer, before receiving cellular therapy – may be replaced by another participant. The new participant will be allocated to the same randomization position as the excluded participant to preserve the balance between treatment groups and the integrity of the randomization. The eligibility of substitutes will be verified according to the same inclusion and exclusion criteria established in the protocol.

During this phase, participants with unstable clinical conditions will be monitored for up to one month. After this period, clinical reassessment will be carried out. If the underlying conditions are resolved, they may be reevaluated for inclusion (Fig 1).

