### Randomization

Randomization will be prepared by a technician, using a random numerical table construction program available at http://stattrek.com/Tables/Random.aspx. Twenty positions will be drawn, with number 1 being fixed for Group 1 (cell therapy) and number 2 for Group 2 (control), randomly and consecutively. The envelope containing the randomization sequence will be held by an independent professional, the study team will not have access to the allocation order until time for adipose tissue collection.

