### Discontinuation criteria – suspension of intervention

Participants will be withdrawn from the study if one of the following occurs:

Major amputation (ankle, leg, or thigh) of the treated limb.Loss of follow-up.Clinical worsening (at the discretion of the investigator).Active ulcer infection.Unfit conditions to be subjected to the cellular therapy procedure within one month after the set date for the procedure.

If a participant’s intervention is discontinued, they will be followed up and encouraged to return for scheduled visits.

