Follow-up of patients will continue for 120 days from the moment they receive treatment with the proposed advanced cell therapy. Time required for screening and preparations will not count toward the study follow-up period. Participants will be reassessed on days 7, 30, 60, 90, and 120 days after randomization. The closing assessment will be carried out after 120 days (assessment 6). After completing their participation in the study, the participants will be referred for routine follow-up at the vascular surgery outpatient clinic of the Clinical Hospital of the Faculty of Medicine of Botucatu. During this period, extra visits may occur, if necessary (S3 File Table 1 Assessment Schedule).

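### The replacement window in Group 1 runs past the point where the arm is revealed, so reusing the randomisation position undermines concealment and conflicts with the stated ITT analysis

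*Protocol article*

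**What the plan says.** All references are to the protocol article.

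- **Participant replacement.** Participants excluded during screening may be replaced. Screening is defined as "the interval between the initial assessment and first reassessment of the arterial ulcer, before receiving cellular therapy". On the substitute: "The new participant will be allocated to the same randomization position as the excluded participant". The section presents this as protecting both the balance between groups and the soundness of the randomisation.
- **Randomization.** An independent professional holds the sequence, and "the study team will not have access to the allocation order until time for adipose tissue collection".
- **Abstract, Methods.** After tissue collection: "These cells will then be expanded in a lab (cell processing center) for 14–21 days before being applied to the lesion".
- **Participant timeline.** "Participants will be reassessed on days 7, 30, 60, 90, and 120 days after randomization".
- **Discontinuation criteria – suspension of intervention.** One ground for withdrawal is "Unfit conditions to be subjected to the cellular therapy procedure within one month after the set date for the procedure".
- **Sample size.** "This study was designed to be analyzed with intention to treat (ITT". The assumed healing rates are 75% and 30%, with 20 participants per group.
- **Study design.** The trial is open-label with blinded endpoint assessment (PROBE).

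**The concern.** A participant whose randomisation position can be inherited already holds one. Removing that participant and giving the position to someone else is harmless only while nobody who recruits knows which arm the position carries. The article does not draw the line there. It draws it at receipt of cell therapy, which in Group 1 comes after the team has learned the allocation.

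Two things are at stake. First, concealment: whoever enrols the substitute can know the arm in advance and, even without intent, choose a patient to suit it. Second, the analysis set: the displaced participant was allocated, and no visible section keeps that person in the analysis, so the comparison is no longer of everyone randomised. The exclusion criteria that operate in this window (active infection, necrosis, major amputation, healed ulcer) are outcomes of the trial or close to them, so the removals are not neutral.

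**Working it through.** **Step 1: order of events in Group 1, from the text**

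1. A randomisation position is held (implied by the replacement rule).
2. Tissue is collected, and the study team may learn the allocation (Randomization).
3. Cells are expanded for 14–21 days (Abstract, Methods).
4. Cells are applied. The replacement window closes before this (Participant replacement).

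The stretch between 2 and 4 is at least 14–21 days. It lies inside the window as worded and after the reveal. The window's other marker, the first ulcer reassessment, does not settle the matter: the Participant timeline counts reassessments from randomisation, with the first at day 7, so that marker can also fall after randomisation. No visible section restricts replacement to unopened allocations.

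**Step 2: the plan's own sample size**

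Inputs (Sample size section): 75% v 30%, two-sided 5%, power 80%. Pooled-variance formula with mean rate 0.525:

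n = [1.96·√(2·0.525·0.475) + 0.842·√(0.75·0.25 + 0.30·0.70)]² / 0.45² = 18.1, so 19 per group.

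The stated 20 reproduces. Exact power at 20 per group is 82.3% by Pearson's test and 73.1% by Fisher's test. The sample size is not in dispute here.

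**Step 3: how far replacement could move the result**

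Assumptions: no treatment effect, 30% true healing in both arms, 20 per group, a share f of Group 1 replaced by average substitutes, none of Group 2 replaced. The documents give no removal rate, so f is shown as a range. If the removed participants would have healed with probability h, expected Group 1 healing becomes

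p₁ = 0.30 − f·h + f·0.30 = 0.30 + f·(0.30 − h).

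With h = 0 (all removals non-healers), the chance of a two-sided p ≤ 0.05 with Group 1 better, from exact binomial enumeration, is:

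| f | p₁ | Pearson | Fisher |
|---|---|---|---|
| 0 | 30% | 2.7% | 1.2% |
| 10% | 33% | 4.2% | 2.1% |
| 20% | 36% | 6.2% | 3.3% |
| 30% | 39% | 8.9% | 5.0% |

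With h = 0.30, p₁ stays at 30% and nothing shifts. With h = 1 (all removals are healed ulcers) and f = 10%, p₁ = 0.30 − 0.07 = 23%, and the bias runs against cell therapy.

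**Step 4: what a proper ITT analysis costs**

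Suppose k of 20 in Group 1 stay in the analysis without receiving cells, and heal at the control rate. Then p₁ = [(20 − k)·0.75 + k·0.30]/20.

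- k = 1: p₁ = 72.75%, exact Pearson power about 78%.
- k = 2: p₁ = 70.5%, exact Pearson power about 73%.

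Both compare with about 82% when all 20 are treated.

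**The case against.** The strongest reply is that the rule speaks of the screening period, and screening normally precedes allocation. If every such exclusion happens with the allocation still sealed, concealment is intact and the ITT conflict is minor. Fig 1 and the S3 assessment schedule, which are not shown, might make that order clear. This stands as a limit on the point but does not remove it: the visible text defines the period by receipt of cells, not by the opening of the allocation.

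Several stronger readings are tempting, and the documents do not support them.

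- *The bias must favour cell therapy.* A healed ulcer during screening is also an exclusion, so removals can push either way.
- *Group 1 participants who worsen or lose the limb while waiting will be swapped out.* The discontinuation section does not mention replacement and says discontinued participants will be followed up. The Data collection plan treats death and amputation as endpoints, not as lost data. The one-month unfitness criterion therefore cannot simply be added to the replacement window.
- *Group 2 has no comparable wait.* The article does not say so. It defines one window for participants generally.
- *False positives of 13% or more.* That size needs substitutes who are themselves filtered for poor prognosis, a 30% removal share and Pearson's test. The article also names Fisher's test.
- *The list itself is unsound.* The Randomization section says "Twenty positions will be drawn, with number 1 being fixed for Group 1 (cell therapy) and number 2 for Group 2 (control". That may mean twenty of forty, and an independent holder could release allocations one at a time. The wording is ambiguous, which does not show a faulty list.

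**Conclusion.** The point holds as a conflict of timing between the replacement rule and the moment of disclosure, and between that rule and ITT. As written, a Group 1 position can be refilled after its arm is known, and an allocated participant can drop out of the comparison. The rule therefore does not protect the randomisation in the way the section says it does.

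The size depends on assumptions that the documents do not supply. If 10–30% of Group 1 were replaced and all of those were non-healers, the false-positive rate favouring cells would be about 1.6 to 3.3 times its baseline by Pearson's test (4.2/2.7 to 8.9/2.7). If removals heal at the background rate the shift is zero, and if they are healed ulcers it reverses. The loss of concealment and the departure from ITT do not depend on those shares; they need only one replacement after the allocation is opened.

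**What to change.** Amend before recruitment:

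1. Complete screening and the pre-treatment ulcer reassessment before the allocation is opened.
2. Allow replacement only for exclusions made before the allocation is opened.
3. Once it is opened, keep the participant in the assigned arm for the ITT analysis, treated or not, and do not reuse the position.
4. Reconcile the timing in the Participant replacement, Randomization, suspension of intervention and Participant timeline sections, so that one sequence of screening, randomisation, tissue collection, treatment and first reassessment applies throughout.

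The wording change costs little, but the statistical cost should be stated openly. Untreated Group 1 participants dilute the effect: one or two of 20 healing at the control rate takes exact Pearson power from about 82% to about 78% or 73%. The power statement should be given with that allowance, and the sponsor should decide whether 20 per group is still enough.
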